**Methods:**

A cohort design will be used. A representative sample of community-dwelling adults with an SMI, including those in care (*n* = 650) and not in care (*n* = 150), will be followed over time. During a two-year time period, participants will be interviewed twice using a wide-ranging set of validated instruments. Interview data will be matched with administrative data about the care process, as retrieved from their patient files. Primary outcomes are changes over time in recovery, societal participation and quality of life, controlled for the occurrence of adverse life-events during follow-up. Additionally, prevalence estimates of and associations between social functioning, safety and discrimination, substance use and health indicators will be investigated.

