##### Safety & discrimination: subjective safety and victimization

Victimization will be measured with the Integral Safety Monitor (ISM) [58]. The instrument is used in the context of a yearly national monitor study of the Dutch Ministry of Safety and Justice, performed by Dutch municipalities. The ISM is a self-report instrument that includes the assessment of neighborhood livability, subjective safety and victimization of 15 different types of crimes among which violent crimes (e.g., battery/assault, sexual violence), nonviolent crimes (e.g., theft, home burglary) and cybercrimes (e.g., identity theft, cyber bullying). The IVM has, to our knowledge, not been tested for its psychometric properties. However, it is considered an adequate and well-structured instrument to gather self-reported information about victimization [58]. Self-report is considered to be more reliable and accurate than using information from objective registries that tend to underreport victimization (e.g., police, public prosecutor) [59].

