##### Substance use & life events: adverse life-events

Based on Brugha’s list of threatening experiences (LTE) [69], that includes 12 distinct negative life-events, the life-time and past year occurrence of negative life-events will be assessed with *yes/no* items. Items are, for example, *having been severely ill or a victim of violence*, *the death of a parent, sibling or child*, and *having been fired*. Besides the separate items, a sum score will be computed with higher scores indicating higher exposure to negative life-events. The LTE is a valid and reliable measure with high test-retest reliability, good agreement with informant information and low internal consistency [70, 71].

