### Primary study outcomes

The study has three primary outcome measures: recovery, societal participation, and quality of life. With respect to recovery, the total score of the National Recovery Scale [77] will be used. Concerning societal participation, two separate indicators will be involved: 1) having formal work/daytime activities (yes/no) and 2) the total score of the Social Exclusion Index for Health Surveys (SEI-HS) [55]. Last, quality of life will be operationalized according to the total score of the MANSA-16 [72].

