Research question 3 will be analyzed using data from the baseline and follow-up measurement by means of generalized linear mixed models with repeated measurements of recovery, quality of life and societal participation as dependent variables. The time between both measures will be included as a within-subjects factor. The same set of predictor variables as mentioned above will be treated as time-dependent independent variables. Additionally, the total score on Brugha’s life-events questionnaire will be included as a potential mediator to assess the effect of having experienced adverse life-events in the time period between baseline and follow-up on the associations between predictor and outcome variables. All variables will be checked for potential outliers. Missing values will be dealt with appropriately. Participants with > 80% missing values on all items will be deleted from the final dataset. For most measures, descriptive analyses will be carried out and the proportion of missing values will be reported for each variable of interest. In subsequent statistical analyses, values missing at (completely) random (i.e. MAR and MCAR) will be deleted pair wise. Values that are not missing at random (NMAR) will be imputed with either the mean, median or using multiple imputation, whichever is most appropriate. Concerning outcome measures that are a sum score of items, instructions from the instrument developers will be followed (e.g., impute missing values with the mean value of the non-missing items and calculate a sum score only if < 10% of items are missing).

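### The 12-item life-events total contains dismissal and violence, so its results for the work indicator and for victimization are partly built in

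*Protocol article*

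**What the plan says.** All references are to the protocol article.

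- **Role of life events.** Under Statistical methods, the total of the "life-events questionnaire will be included as a potential mediator to assess the effect of having experienced adverse life-events" enters the mixed models of recovery, quality of life and societal participation. The abstract (Methods) describes changes in the primary outcomes as "controlled for the occurrence of adverse life-events during follow-up".
- **Content of the score.** The adverse life-events section describes a list "that includes 12 distinct negative life-events", scored yes/no. Its examples include "having been severely ill or a victim of violence" and "having been fired". The separate items are kept and a sum is computed.
- **Outcome side.** Under Primary study outcomes, societal participation has two indicators, one of which is "having formal work/daytime activities (yes/no)". The other primary indicators are the totals of the National Recovery Scale, the SEI-HS and the MANSA-16.
- **Predictor side.** Under Statistical methods, victimization is one of the predictors, and the same set is carried into the longitudinal models as time-dependent variables. The section on subjective safety and victimization says that the measure covers 15 types of crime, among them "violent crimes (e.g., battery/assault, sexual violence)".

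No section removes a shared item from the total or plans an analysis without it.

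**The concern.** A mediator, or a covariate that outcomes are adjusted for, should be measured separately from both the predictor and the outcome. Here it partly is not.

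In the work model, a dismissal adds one point to the life-events total and can itself be the event that changes the outcome from yes to no. Some association between life events and work then arises even if no other event has any influence, and the adjusted change over time is adjusted for a piece of the outcome.

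In any model with victimization, one assault can be counted in the predictor and again in the supposed mediator. The victimization coefficient falls when the total is added, and the fall could be reported as an effect running through adverse life events although it is the same event measured twice.

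**Working it through.** The protocol gives no figure to reproduce on this point. The overlap follows from setting the sections above side by side. Its size can only be illustrated, and **every prevalence below is an assumption**.

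**1. Weight of the two items in the total.** For 12 independent yes/no items, r(item, total) = √[p(1−p) / Var(total)].

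- Equal prevalences: r = 1/√12 = 0.29 for each item, and the two items carry 2/12 = 16.7% of the variance.
- Example with ten other items at 10%, dismissal 5% and violence 10%: Var = 10 × 0.09 + 0.0475 + 0.09 = 1.0375. The two items carry (0.0475 + 0.09)/1.0375 = 13%. The correlations with the total are 0.21 (dismissal) and 0.29 (violence).
- Other items 5–20%, dismissal 2–10%, violence 5–20%: the two items carry about 4% to 35%.

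**2. Work indicator, adjusting for baseline work.** Model: logit P(work at follow-up) = a + b × baseline work + c × life-events sum. Assumed: 30% working at baseline, 10% or 20% of workers dismissed, and eleven other events at 10% each with no effect on work. The true odds ratio for those events is 1.00. z is scaled to n = 800, the planned baseline sample, with no loss to follow-up.

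| Dismissed people back in work or activities | 10% of workers dismissed | 20% of workers dismissed |
|---|---|---|
| none | 0.81 (z about −2.0) | 0.70–0.71 (z about −3.3) |
| 50% | 0.90 (z −0.9) | 0.84 (z −1.6) |
| 60% | 0.93–0.94 (z −0.6) | 0.89 (z −1.0) |

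Without the dismissal item the odds ratio is 0.99 to 1.01. Background movement in and out of work also matters (10% each way in the 50% row): less of it moves the ratio further from 1.

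**3. Work indicator, repeated measures.** A model with both measurements as dependent variable, closer to the one planned, gives about 0.90 to 0.98 per event under the same assumptions, and about 1.00 without the item. Specification matters because only people with a job can be dismissed:

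- If follow-up work is analysed with no account of baseline work, the odds ratio is 0.92 to 1.05.
- In a related simulation (20–40% working at baseline, 10–25% of workers dismissed, 0–60% of those back in work), the whole-sample correlation between total and follow-up work is only −0.06 to +0.05, against −0.17 to −0.39 among those working at baseline.
- For within-person change in work, the spurious slope is negative throughout, −0.01 to −0.06 per event.

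**4. Victimization.** Assumed: true effect −0.30 SD, each other event −0.10 SD, and no separate effect of the violence item. If 25%, 50% or 80% of victims also endorse that item, the coefficient with the full total is about −0.28, −0.255 or −0.22. The apparent mediation is 0.02/0.30 = 7%, 0.045/0.30 = 15% or 0.08/0.30 = 27%, although none is present. Without the item the coefficient stays at about −0.30. With other events at −0.05 SD and 50% endorsement it falls only to −0.28.

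**The case against.** The strongest reply is that the overlap is partial and its effect may be small. A dismissed person may have new work or daytime activities two years later. A person without work need not have been dismissed. Victimization also covers non-violent crime and cybercrime. The life-events list asks about the past year as well as lifetime, while the interviews are two years apart. If only half of dismissals are captured, the odds ratios with nobody back in work are 0.89 (z −1.1) and 0.84 (z −1.7), and with half back they are 0.95 and 0.91. All of this stands, and it limits the size of the problem without removing it.

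A second reply is that using an instrument's published total is normal and that item-level choices belong in an analysis plan. This carries less weight: the protocol has already fixed the covariate as the total score, so the issue is a stated choice and not an omitted detail. It is true that a modified sum is less comparable across outcomes and with published totals.

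A third reply also stands. The article's example joins severe illness and violence, so it does not show whether the instrument has a separable violence item. Dropping that item outright could discard a genuine adverse event.

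A reader might infer that the life-events score explains the primary outcomes by definition, or that life events are bound to appear to reduce participation. The documents do not support either. Two of 12 events are involved, the dismissal overlap reaches one of four primary indicators, and the spurious association is often too weak to be significant at 800 participants.

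**Conclusion.** The point holds in a limited form. The planned total overlaps partly with the work or daytime-activities indicator, through dismissal, and with the victimization predictor, through violence. Adjustment and mediation results for these two variables are therefore contaminated.

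Under the assumed prevalences, the built-in odds ratio per event for work is about 0.70 to 0.94 with adjustment for baseline work, and about 0.90 to 0.98 in a repeated-measures model. The lower end requires that nobody dismissed is back in work or activities, and incomplete capture of dismissals brings the ratio closer to 1. For victimization, roughly 7% to 27% of the effect could be misread as mediated, if the violence item has no effect of its own.

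The existence of the overlap rests on the protocol's text; its size does not, because the protocol gives no rate of employment, dismissal or victimization. The recovery, social exclusion and quality-of-life totals are not shown to share an item with the life-events list. Their models are affected only through the victimization term.

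**What to change.** - **Work or daytime-activities model:** compute the life-events sum without the dismissal or job-loss item(s), and report dismissal descriptively as one way in which work was lost.
- **Models containing victimization:** check on the instrument whether violence is separate from severe illness. Add a sensitivity analysis that leaves out the item covering violence. Do not read a fall in the victimization coefficient as mediation if it disappears in that analysis.
- **All of these models:** show the result with the full 12-item total alongside, for comparability.

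The cost is a few sentences of analysis wording and some extra model runs; the items are already collected and kept separately. The downside is that the sum differs from the published total and between outcomes, which the parallel full-total results make visible.

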With respect to the in-care and not-in-care cohorts, their relative proportions within the total SMI-population in Amsterdam are approximately 76 and 24%, respectively [30]. Furthermore, around 90% of both groups lives independently (i.e. community dwelling). In-care participants will be recruited at the two largest mental health care providers in Amsterdam, Arkin and GGZ inGeest. Together, these organizations are estimated to provide care/treatment to two thirds of the total in-care population of people with an SMI in Amsterdam [39]. The remaining 33% of the in-care SMI-population, those who receive mental health care from one of several other (small) providers, will not be included as we expect to obtain a representative sample of the in-care population from the selected service providers. Moreover, recruiting participants at numerous care providers would require a disproportional effort and is therefore considered unfeasible. The ‘not-in-care’ participants will be recruited at a variety of social welfare and social support organizations in Amsterdam, including organizations that target the homeless (e.g., HVO-Querido, Leger des Heils, Cordaan, Volksbond). In this group, the SMI-criteria will be assessed during the interview.

As such, on the basis of 1) the assumed average SMI prevalence of 1.6% among the adult population of the selected quarters (237,157 * 1,6% = 3795 people), and 2) the proportion of adults with an SMI who are registered as a mental health care patient (76%, *n* = 2884), and 3) of whom at one of the two main mental health care providers in the city (66%, *n* = 1903) and 4) the proportion within this group who live independently (i.e. community dwelling) (90%), the in-care cohort is estimated to consist of 1739 adults with an SMI. On the basis of the aforementioned proportions, the not-in-care cohort is estimated to consist of 820 people. The LZA-cohort potentially consists of 157 former LZA-participants who gave permission to be re-approached. Based on expected response rates of 33% in the in-care cohort, 20% in the not-in-care cohort and 50% in the LZA-cohort, the study sample will consist of approximately 800 participants. Figure 1 presents a flowchart depicting the composition of the study population.

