### Statistical methods

All cross-sectional socio-demographic data from both baseline and follow-up measurements will be reported in terms of percentages, means with standard deviations, and quartiles. In addition, all study measures (from the instruments administered and from the registry data) will be analyzed descriptively to provide estimates of the relevant proportions within our study population with respect to these variables as (partial) answers to research questions 2, 4 and 5.

In addition, to provide information on the association between experienced need, and the primary outcome variables (research question 1), data collected at baseline will be analyzed using multivariate regression with recovery, societal participation and quality of life as separate dependent variables and total scores on the CANSAS (i.e. number of unmet needs for care), discrimination scale, stigma scale and victimization as independent (predictor) variables. Any potential mediating effects on the associations between predictors and outcomes variables will be investigated by adding age, sex, psychiatric symptoms (BPRS-E), harmful/dependent alcohol and/or drug use (AUDIT and DUDIT respectively), physical health (RAND SF-36) and city-districts as covariates in these analyses.

To answer research question 2, relationships between the outcome measures and distinct CANSAS items, registry data concerning the care process (i.e. treatment compliance, therapeutic alliance, frequency and timeliness of care consults and self-reported support for social problems) from mental health institutions and support/welfare organizations will mainly be reported in terms of percentages and, for obvious comparisons between groups, using regression models and chi-squared tests. Their associated proportion of variance explained Nagelkerke’s R^2^, Phi for 2 × 2 tables and Cramer’s V for larger than 2 × 2 tables will be reported. Phi and Cramer’s V will be interpreted as indicating no or very weak (> 0), weak (>.05), moderate (>.10), strong (>.15) or very strong (>.25) association between variables [93]. Eta-squared and Cohen’s D will be interpreted as very small (0–.19), small (.20–. 49), moderate (.50–.79), large (.80–1.20), very large (1.20–1.99) or huge (2.0) [94].

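### The missing-data rules match the wrong method to the mechanism: MAR values are deleted pairwise, and NMAR values get mean, median or standard multiple imputation, none of which corrects NMAR

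*Protocol article*

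**What the plan says.** The end of Statistical methods in the protocol article sets two rules, one after the other:

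- MCAR and MAR: "values missing at (completely) random (i.e. MAR and MCAR) will be deleted pair wise".
- NMAR: "Values that are not missing at random (NMAR) will be imputed with either the mean, median or using multiple imputation, whichever is most appropriate".

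The opening words, "In subsequent statistical analyses, values missing at (completely) random", place the deletion rule after the descriptive step. It therefore covers both model families:

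- the baseline models, where "data collected at baseline will be analyzed using multivariate regression with recovery, societal participation and quality of life as separate dependent variables";
- the two-wave models, fitted "by means of generalized linear mixed models with repeated measurements of recovery, quality of life and societal participation as dependent variables".

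Two neighbouring rules are separate and are not in dispute. Sum scores follow the instrument developers, for example "impute missing values with the mean value of the non-missing items and calculate a sum score only if < 10% of items are missing". Almost empty records are removed: "Participants with > 80% missing values on all items will be deleted from the final dataset".

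The article does not say how a value is to be classed as MAR or NMAR, how to choose among the three imputation options, or that the mixed model takes the place of deletion for MAR outcomes.

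**The concern.** Each mechanism is given a method that does not suit it. Under MAR, missingness is explained by observed data such as the baseline score, symptoms or cohort. Deletion discards that information, whereas standard multiple imputation and likelihood methods use it. Under NMAR, missingness depends on the unseen value itself. Mean, median and standard multiple imputation all fill in values as if it did not.

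The rule also turns on a distinction that the data cannot make. The same observed values are compatible with a MAR and an NMAR explanation, so the analyst must decide by judgement, and the wording of the NMAR rule then leaves three methods open.

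The affected models carry the primary outcomes: recovery, societal participation and quality of life, measured two years apart. Missingness that is completely at random cannot be taken for granted. The section on recruitment at the first provider itself foresees missed appointments because of sickness or mental instability. This is a stated rule, not detail left for later, and an analysis plan that followed it would carry the error forward.

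**Working it through.** The article gives no missing share, attrition rate or correlation, so there is no figure of the plan's own to reproduce. The only documented number used is the sample size: "the study sample will consist of approximately 800 participants". Check: 0.33 × 1739 + 0.20 × 820 + 0.50 × 157 = 573.9 + 164.0 + 78.5 = 816, which agrees.

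**Assumed inputs (not in the article).** Scores in SD units; wave correlation 0.6; true slope of outcome on predictor -0.40; 30% missing, with 20% where shown; logistic missingness with the slopes given.

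**1. Rule against mechanism**

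| Mechanism | Rule in the article | Valid? |
|---|---|---|
| MCAR | deletion | yes; simulated bias 0.00, coverage 94-95% |
| MAR | deletion | only in special cases, e.g. a regression where missingness depends only on modelled covariates |
| NMAR | mean or median imputation | no; bias stays and the standard error shrinks |
| NMAR | standard multiple imputation | no; bias is reduced but stays |

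**2. Deletion when predictor missingness depends on the outcome** (30% missing, logit slope 0.7 to 1.5). The slope of -0.40 becomes -0.37 to -0.32. If missingness depends only on covariates in the model, it stays at -0.40.

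**3. Mean imputation of an NMAR outcome** (30% missing, logit slope 0.5 to 1.0). The slope of -0.40 becomes -0.27 to -0.24. At logit slope 1.0, deletion gives a slope of size 0.35, so mean imputation (0.24) does more harm to the association than deletion. At 20% missing the sizes are 0.36 under deletion and 0.28 under mean imputation.

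The familiar result 0.70 × (-0.40) = -0.28 at 30% is the MCAR case. It does not describe this plan, which deletes MCAR values.

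Standard error of the mean with a fraction p imputed at the observed mean:

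- complete case: s / √((1 - p)N)
- mean-imputed: s√(1 - p) / √N
- ratio: 1 - p = 0.70 at p = 0.30, and 0.80 at p = 0.20

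**4. Follow-up mean under MAR** (30% missing, logit slope 0.5 to 1.0 on the baseline score, no true change). Let m be the baseline mean of those who remain.

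- All baseline values against remaining follow-up values: 0.6m. With m = 0.15 and 0.25 this is 0.09 and 0.15 SD too high.
- Completer pairs only: 0.6m - m = -0.4m, that is 0.06 and 0.10 SD too low.
- Likelihood on all available outcomes: 0.00.

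**5. Multiple imputation** (N = 800, 1,500 replicates, logit slope 1, follow-up mean).

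- Under MAR, bias falls from 0.11 to 0.00 SD at 20% missing and from 0.15 to 0.00 SD at 30%. Coverage of the 95% interval rises from 22% to 96% and from 4% to 95%. These figures concern a raw follow-up mean, not the mixed model.
- Under NMAR, bias is 0.18 and 0.26 SD with mean imputation, and still 0.12 and 0.17 SD with multiple imputation. The reported standard error is 0.80 and 0.71 of the true one with mean imputation, against 0.99 and 1.03 with multiple imputation.

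**The case against.** The other side has several good points.

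- **The mixed model may already cope.** Fitted by likelihood on every available outcome, it is valid for MAR outcomes. This stands, and step 4 shows it. A reader might infer that the longitudinal results must show a false improvement. The documents do not support that: the sign of the error depends on whether all values or completer pairs are compared, and the likelihood model shows none. What remains is that the article states deletion for MAR without exempting these models, and rows with missing time-dependent predictors would still be lost.
- **Deletion is harmless when missingness depends on modelled covariates.** This stands. Symptoms, substance use, physical health, age, sex and district are planned as covariates. The rule, however, is not limited to that case.
- **Intervals.** A reader might infer that the rules as a whole make intervals too narrow. Only mean or median imputation does so; deletion and proper multiple imputation do not.
- **Pairwise deletion.** It might be called undefined for mixed models. That holds only for the strict covariance-matrix sense. Read as available-case use in each analysis, it can be applied.
- **Scale totals have their own rule.** Three of the four primary indicators are total scores, so mean imputation of a primary outcome would matter mainly for wholly missing scales, and it is one of three options. This limits how often the harm arises but does not make the option valid.
- **Much of the reporting is descriptive.** This is true, but the regressions and mixed models are planned analyses of the primary outcomes.

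**Conclusion.** Wrong as written. The article pairs MAR with a method that is valid in general only under MCAR, and NMAR with methods that do not correct it. It also makes the choice depend on a distinction that the observed data cannot settle. No other part of the article repairs this. The MCAR half of the deletion rule and the item-level scoring rules are sound.

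In size, with 30% missing, the harm is an association weakened from -0.40 to between -0.37 and -0.32 by deletion in the unfavourable case, and to between -0.27 and -0.24 by mean imputation of an NMAR outcome, with a standard error of the outcome mean 30% too small relative to complete cases. These figures depend on the assumed missing share, correlation and logit slopes. They show direction and order of magnitude and do not forecast this cohort. The defect in the rule itself needs none of these assumptions.

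**What to change.** Replace the two sentences; merely exchanging the two rules would not suffice, because NMAR needs its own treatment.

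- Baseline regressions: multiple imputation under MAR, with the outcomes, predictors and covariates in the imputation model.
- Mixed models: maximum likelihood on all available outcomes, with multiple imputation of missing time-dependent predictors.
- Remove mean and median imputation of whole variables. Keep the developers' item-level scoring rules.
- Treat NMAR as a sensitivity analysis on top of the imputation, for example delta-adjusted, not as a class of values to be identified in the data.

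The cost is new wording and modest extra analysis time. Intervals will be wider than under mean imputation. Recruitment and data collection do not change.
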